##### Healthcare resource use

The costs arising from catheterization, such as the consumption of consumable materials and resources and diagnostic tests (urine cultures and catheter cultures and biofilm analysis), will be collected in the Patient's Clinical Data Notebook and will be evaluated from the public healthcare services perspective. The analysis will also include costs because of patient contacts with primary care services, hospital admissions and length of stay, outpatient visits, emergency attendance, and medications prescribed during the study period. The information related to healthcare resource use will be drawn from each patient's electronic clinical record.

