##### Magnitude of infections

The magnitude of infection will be obtained from the analysis of urine culture samples taken from patients twice, during inclusion (time 0) and during withdrawal of the catheter (time 4 weeks; Table 1). In the event that the patient is prescribed an antibiotic for a UTI before the 28th day, the magnitude of infection will be evaluated at the time of prescription, through the analysis of a urine culture sample, according to usual clinical practice. The research staff will take between 5 and 10 mL of urine sample in a sterile container which will be transported to the laboratory in the shortest time possible (<2 h). If the transport or processing cannot be performed immediately, the sample will be refrigerated between 2°C and 8°C without exceeding 24 h until processing. The second urine sample will be collected from the new catheter inserted at the follow‐up visit. After seeding the urine in specific culture media, the microorganisms that have grown in the culture will be analysed to determine the number and type of microorganisms present using techniques based on biochemical tests and Matrix‐Assisted Laser Desorption/Ionization Time‐Of‐Flight (MALDI‐TOF) type mass spectrometry.

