##### Rate of symptomatic and asymptomatic infections

The magnitude of infection obtained from the urine samples will be classified according to the following criteria based on the European Association of Urology (EAU) clinical guidelines^29^:
Symptomatic infection: The presence of pathogenic microorganisms in amounts greater or equal to 1000 Colony Forming Units/mL (CFU/mL) accompanied with symptoms will determine the existence of the infection.Asymptomatic infection: In the absence of infection symptoms, a quantity of microorganisms greater than or equal to 100 000 CFU/mL will indicate asymptomatic infection.

In addition to the presence or absence of infections to assess their rate, this variable will also be collected using the outcome measure “infection‐free days” (with a maximum possible value of 28 days) to be compared between Foley‐type catheters and T‐Control. Suppose the patient at some point prior to the follow‐up visit presents symptoms compatible with UTI. In that case, a urine culture will be performed to confirm the presence or absence of urinary infection, according to usual clinical practice. In the event that the patient receives an antibiotic for a UTI while he/she takes part in the study prior to the follow‐up visit, this will be recorded in the medical record. However, the patient will also be asked about it at the follow‐up visit when he hands in his/her incident diary, and this will be counted as an infection.

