##### Determination of the biofilm formed in the catheters and identification of the microorganisms present

The catheter removed will be sent to the laboratory, and with the help of sterile gloves and scissors, a 1 cm‐sized fragment corresponding to the part below the balloon will be cultured for each catheter to assess whether biofilm is present or absent. The microorganisms forming the biofilm will be quantified as CFU per catheter piece. These microorganisms will also be identified by means of MALDI‐TOF‐type mass spectrometry to establish statistical relationships with those identified in the urine cultures. In the event that during the course of the 14 days in which the patient will be catheterized, he receives antibiotic treatment due to a UTI, this will be taken into account when analysing the results obtained in the catheter's biofilm determination.

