#### Cost‐effectiveness analysis

5.7.1

An economic evaluation of T‐Control versus the conventional Foley catheter from the public healthcare services perspective will be performed according to the analytical methods accepted by the scientific community.^32^ The cost‐effectiveness measure will be the incremental cost per quality‐adjusted life year (QALY) gained. QALYs are a generic health measure that combines information on life expectancy with the patient's quality of life. QALYs will be calculated based on the health‐related quality of life data collected according to the EQ‐5D‐5L instrument which will be collected for each patient. The time horizon will be the study duration. Costs included in the analysis will be those incurred by the public healthcare service. Unit costs will be obtained from the hospital centres accounting records whenever possible, from the eHealth cost database (Oblikue Consulting), and from national public sources. The mean total cost of each intervention evaluated will be presented using basic descriptive statistics (means, medians, and measures of variability such as variance).

Cost‐effectiveness will be calculated as the incremental cost‐effectiveness ratio which results from dividing the difference in costs between interventions by the difference in effects observed (QALYs). Nonparametric methods based on bootstrapped simulations will be used to calculate the confidence intervals around the incremental cost‐effectiveness ratio. In addition, the same nonparametric methods will be used to construct a cost‐effectiveness acceptability curve that will reveal the probability that each alternative is cost‐effective for different cost‐effectiveness thresholds (willingness to pay for an additional unit of effectiveness). Finally, deterministic sensitivity analysis (one‐way, two‐way, and multiway) will be performed with the aim of analysing the impact of the parameters on the cost‐effectiveness results. The analysis will be performed using the software R and the statistical package STATA (StataCorp LLC, College Station, USA).

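### Protocol-scheduled cultures and biofilm assays are costed together with clinically indicated tests, which overstates the mean cost reported for each arm relative to routine care

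*Protocol article*

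**What the plan says.** Section 5.4.2, Healthcare resource use, lists the catheterization costs to be collected in the Patient's Clinical Data Notebook. Besides consumables, the list contains "diagnostic tests (urine cultures and catheter cultures and biofilm analysis". These costs "will be evaluated from the public healthcare services perspective".

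Section 5.7.1 adds a general rule, "Costs included in the analysis will be those incurred by the public healthcare service", and makes the cost per arm an output in its own right: "The mean total cost of each intervention evaluated will be presented using basic descriptive statistics". The incremental cost per QALY is then built on the difference in cost between arms.

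Other parts of the article show when the tests are done:

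- **Urine culture.** Under Magnitude of infections, samples are "taken from patients twice, during inclusion (time 0) and during withdrawal of the catheter". Table 1 shows the same two time points.
- **Catheter culture.** Under Determination of the biofilm, a fragment "will be cultured for each catheter to assess whether biofilm is present or absent". Table 1 places this at 4 weeks.
- **Clinically indicated culture.** Under Rate of symptomatic and asymptomatic infections, if symptoms appear before the follow-up visit, "a urine culture will be performed to confirm the presence or absence of urinary infection, according to usual clinical practice". Magnitude of infections uses similar words for a culture taken when an antibiotic is prescribed for a UTI.

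**The concern.** The article already distinguishes two kinds of test. Cultures prompted by symptoms or by a UTI prescription are described as usual practice. The inclusion culture, the 4-week culture and the catheter culture are set by the trial timetable and feed the secondary endpoints. The cost list does not carry this distinction over.

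A health service that adopted either catheter would not, on anything the article says, culture a piece of every removed catheter. Nor would it take a urine culture from every symptom-free patient at insertion. The eligibility criteria require absence of infection symptoms, so the inclusion culture cannot have been prompted by symptoms. If these tests are priced, the reported mean cost per arm describes the trial and not the care that a payer would fund. Mean cost per arm is a planned output, so the error in it remains even where it cancels in the difference between arms.

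**Working it through.** The article states no cost, so there is no figure of its own to reproduce. The check asks how large the scheduled component is and where it survives.

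**Inputs**

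- Scheduled urine cultures per completer: 2 (Magnitude of infections; Table 1).
- Catheter/biofilm cultures per completer: 1 (Determination of the biofilm). The cost list names catheter cultures and biofilm analysis separately, but the methods describe one culture of one fragment, so I count one item.
- Patients per arm: 25; planned dropout: 5% (section 5.3).
- Unit costs: not given. Assumed ranges are U = 10 to 30 per urine culture and B = 20 to 100 per catheter/biofilm culture, in currency units.

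**Step 1. Overstatement per completer = 2U + B**

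| U | B | 2U + B |
|---|---|---|
| 10 | 20 | 40 |
| 20 | 50 | 90 |
| 30 | 100 | 160 |

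**Step 2. Arm mean at the planned 5% dropout.** This step assumes that leavers' partial costs are kept. A leaver has the inclusion culture but not the 4-week one. Whether the catheter is assayed depends on whether an early-removed catheter goes to the laboratory. The arm mean is 0.95(2U + B) + 0.05 × (U or U + B).

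- U = 10, B = 20: 0.95 × 40 + 0.05 × 10 = 38.5, or 0.95 × 40 + 0.05 × 30 = 39.5.
- U = 30, B = 100: 0.95 × 160 + 0.05 × 30 = 153.5, or 0.95 × 160 + 0.05 × 130 = 158.5.

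Planned dropout therefore lowers the overstatement by only 0.5 to 6.5 units.

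**Step 3. Difference between arms**

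- Equal completion: the scheduled component is the same in both arms and the difference is 0.
- Unequal completion, with leavers' partial costs kept: the shift is (difference in dropout) × (U or U + B), in favour of the arm with more leavers.
  - Assumed 10% against 0%: from 0.10 × 10 = 1 to 0.10 × 130 = 13 units.
  - Assumed 20% against 5%: from 0.15 × 10 = 1.5 to 0.15 × 130 = 19.5 units.
  - One extra leaver in an arm of 25: from 10/25 = 0.4 to 130/25 = 5.2 units.

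**The case against.** **The cost list may mean only indicated tests.** It says urine cultures without calling them scheduled, and cultures prompted by symptoms do belong in the cost base. An article may also leave costing detail to the full protocol or the analysis plan. This stands for part of the urine cultures. It does not cover the biofilm analysis, which is named in the list and is nowhere described as usual care. A later plan would have to depart from the list, not merely add detail.

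**Including the tests need not conflict with the stated perspective.** A reader might infer a contradiction with the public healthcare perspective, but the documents do not support one. Perspective concerns who bears a cost, and the article does not say who pays for the assays. If a public hospital laboratory bears them, they are public costs. If the sponsor pays, the general rule in 5.7.1 already removes them. What is left is an unclear costing choice.

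**Early leavers and the cost-effectiveness ratio.** A reader might also infer that patients who leave early will look cheaper and that this will distort the ratio. That is not established, for three reasons:

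- The biofilm section refers to the catheter removed and does not restrict the assay to 4-week removals.
- Section 5.6 sends leavers' data to a substudy analysis, and their place in the cost analysis is not stated.
- EQ-5D-5L is scheduled only at baseline and 4 weeks, and section 5.7 rules out imputation. A leaver without the second questionnaire has no QALY and would normally drop out of a patient-level analysis of cost and QALY.

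Even if a shift arose, its effect on the ratio would rest on assumptions throughout. With an assumed EQ-5D difference of 0.5 SD, an SD of 0.25 and linear change over 28 days, the QALY difference is (28/365.25) × 0.5 × 0.5 × 0.25 = 0.0048. One unit of cost would then move the ratio by about 209 per QALY. On the same inputs the standard error is (28/365.25) × 0.5 × 0.25 × √(2/25) = 0.0027, and the 95% interval of about −0.0005 to 0.0101 includes zero. The ratio is then too unstable for such a shift to matter.

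**Conclusion.** The point holds as a minor one about the mean cost reported for each arm. Followed as written, the cost list adds trial-driven tests to both arms and overstates mean cost relative to routine care by about 40 to 160 units per completer. The direction follows from the text, provided that the tests are priced as listed and are not dropped because someone other than the public service pays. The size rests entirely on the assumed unit costs.

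The incremental cost is unaffected when completion is equal. It shifts only slightly if completion differs and leavers' partial costs stay in, and the article states neither. Cost-effectiveness is a secondary objective, described as preliminary, in a 50-patient pilot, so the consequence is limited.

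**What to change.** Add one sentence to Healthcare resource use (5.4.2) and to 5.7.1: the base-case cost includes only cultures prompted by symptoms, by a UTI prescription or by usual care; the protocol-scheduled inclusion and 4-week urine cultures and all catheter cultures and biofilm assays done for the study are excluded. Add that a scheduled culture which would have been taken anyway, for example because the patient has symptoms at the 4-week visit, stays in. If the sponsor wants the study tests shown, report them on a separate line or in a sensitivity analysis.

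The notebook already collects the tests. The one practical requirement is that each culture be marked as scheduled or clinically indicated. The change needs no new patient procedure, discards no data and does not affect the clinical endpoints.

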##### Level of satisfaction and workload of health professionals

The following instruments are administered to health professionals:
NASA Task Load Index^30^: This is a subjective, multidimensional, and widely used evaluation tool that qualifies the perceived workload to evaluate the effectiveness of a task, system, equipment, or other performance aspects. The questionnaire evaluates six dimensions (mental, physical and temporal demand, performance, effort, and frustration) which enables rating them on a 1 to 10 scale, 1 being the lowest score and 10 the highest score.Health professional satisfaction questionnaire: The questionnaire is specifically devised and based on the experience of previous LivingLab studies^24^ to quantitatively measure satisfaction with the devices used by health professionals (conventional Foley and T‐Control catheters). This questionnaire includes an initial section with 12 statements regarding the catheter insertion process. Health professionals will rate these statements for both devices used during the clinical trial on a 1 to 5 scale according to whether or not they agree with the statements. The second section is intended for health professionals to make a comparison between both devices by means of 11 statements for which they will have to indicate which device best fits these statements according to their opinion. They can only choose one device for each statement. Finally, the questionnaire consists of a free section in which health professionals can write any comments or suggestions. The usability of the device by professionals will also be also tested, verifying that the packaging is adequate and the instructions are understandable and contain all the information necessary to use the device safely.

Baseline data for subjects such as sociodemographic (age, sex, education level, marital status, coexistence, and type of health system user) as well as clinical (diagnostic, symptoms, and previous use of bladder catheter and its accessories) and risk factors and toxic habits data (smoking habits, alcohol consumption, and sedentary lifestyle) were collected.

### Data management

5.5

The data will be stored in a secure computer database and kept confidential in accordance with Europe Union and Spanish Data Protection Legislation (General Data Protection Regulation and the Data Protection Act 2018). Personal data are not kept longer than necessary for the purpose for which it is processed. Access rights to the data set are managed. The principal investigator of the centre and the research coordinator will have access to the full data set to enable analysis at the trial end, while the trial statistician, who is part of the CRO, will only have access to the participants' code. Authorized representatives or competent authorities will gain access to those portions of the medical records relevant to the clinical research by means of cross‐reference with clinical research personnel to verify the data if required. All computerized data will be identified solely by a code. All essential data and documents will be kept for a period of at least 10 years after the trial ends.

The personnel in charge of monitoring will enter the data collected by the research team at the centres into the study database. Safety data, case report forms, and subject questionnaires, as well as biological sample results, will be entered into the database. Monitoring staff will work closely with the research teams at the centres to ensure that the data are as complete and accurate as possible. Data quality is improved by means of a wide range and consistency checks included in the monitoring activities.

The discussion groups will be performed by researchers with experience in qualitative research. The data will be added to the database by the staff in charge of monitoring.

### Oversight and monitoring

5.6

An independent CRO will be in charge of monitoring the clinical trial. This CRO includes staff with clinical, statistical, and methodological expertise. The Sponsor will meet with the CRO after every monitoring visit at the centre to ensure the trial is executed and carried out properly, make recommendations, and report any event that has to be passed on to the Ethics Committee or the competent regulatory health authorities.

There are no scheduled interim analyses for efficacy or futility. However, during the clinical study, the external monitor will have regular contact with the centres where the study is performed. These contacts will include visits to confirm that the facility is in accordance with specified standards and that the clinical research teams are performing the procedure as directed, as well as trial progress and any safety issues.

Retention of subjects is promoted by regular contact with the staff responsible for the study and ensuring adequate outcome measures collection. All data collected are retained and used in the analysis. Data from subjects who terminate the study earlier will also be included in a substudy analysis.

Deviations from the allocated study will be recorded in the case report forms and evaluated as a secondary endpoint.

### Analysis plan

5.7

A statistical analysis plan will document the scheduled analysis, to be finalized before the data lock. The final analysis will take place after full recruitment and follow‐up, at the end of the study.

The analysis population will consist of all patients who meet the selection criteria and are randomized. All patients included in the study and excluded from the analysis will be listed along with their reason for exclusion. Additionally, additional analysis will be performed on patients who complete 4 weeks with the catheter. Subjects who withdraw from the study for any reason after signing the informed consent will not be replaced. No imputation will be made for missing data.

Descriptive statistics will be carried out on the variables under study, using frequencies and percentages for qualitative variables and mean with standard deviation for quantitative variables that follow a normal distribution; otherwise, the median and interquartile ranges will be calculated.

A bivariate analysis will be carried out between the control–study groups with respect to the independent variables to know the comparability of the groups using the Chi square tests for qualitative variables and for the quantitative variables *t*‐Student or Mann–Whitney U, depending on the normality of the sample. All are under a 95% confidence interval and considering statistically significant results with a *p*‐value < 0.005.

In the event that the results are discordant, deviations and/or violations of the protocol will be analysed. For all analyses, the SPSS 24.0 statistical package^31^ will be used and will be carried out by a person who will not know if the patients have been in the intervention or control group.

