#### Criteria for discontinuing or modifying allocated interventions

5.2.1

Reasons for going off or discontinuing the trial are as follows:
Adverse events that may compromise the patient's safety;Need for antibiotic treatment for a reason unrelated to the use of a bladder catheter;The patient's refusal to continue (in the event that, according to clinical practice, they still needed to carry an indwelling bladder catheter, the T‐Control catheter would be exchanged for the conventional Foley‐type catheter); andDeath.

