### Methods of data collection

5.4

The source and timing of measures are summarized in Table 1. In accordance with the proposed research objectives, the outcome measures that will be performed are the following.

**TABLE 1 bco2313-tbl-0001:** Source and timing of variables obtained for the study.

Variable	Method of obtention	Data collection format	Source	Timing			
				Baseline	4 weeks	Up 6 months AFUV	Close‐out
Baseline data (sociodemographic, clinical, and life habits)	Personal interview/PCDN	Paper/electronic	P and HP	X			
Magnitude of infection	Urine culture/PCDN	Paper/electronic	Microbiology laboratory	X	X		
Rate of infection (asymptomatic and symptomatic UTI)	Urine culture/PCDN	Paper/electronic	Microbiology laboratory	X	X		
Adverse events during catheter insertion	Observation/PCDN	Paper/electronic	HP	X			
Adverse events during catheterization time	ID/PCDN	Paper/electronic	P		X		
Catheter biofilm	Viable cells counting/PCDN	Paper/electronic	Microbiology laboratory		X		
Antibiotic treatments related to catheterization	ID/PCDN	Paper/electronic	P and HP		X		
Healthcare resources utilization	ID/PCDN	Paper/electronic	P and HP		X		
Quantitative data for QoL and catheter satisfaction	Patients' questionnaire and EuroQoL 5D questionnaire	Paper/electronic	P	X	X		
Qualitative findings for acceptability and experience	Discussion groups	Audio recording	P			X	
Catheter opinion (professionals)	Professional questionnaire	Paper/electronic	HP				X
Workload perceived	NASA‐TLX questionnaire	Paper/electronic	HP				X

Abbreviations: AFUV, after follow‐up visit; EuroQoL 5D, EuroQol questionnaire—five dimensions—five levels; HP, health professional; ID, incident diary; NASA‐TLX, NASA Task Load Index questionnaire; P, participant/relative, friend, or informal carer‐completed questionnaire; PCDN, Patient Clinical Data Notebook; QoL, quality of life perceived; UTI, urinary tract infections.

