##### Self‐perceived health‐related quality of life

The following instruments are administered to patients:
EQ‐5D‐5L^27^: This is a generic health‐related quality of life questionnaire that evaluates five domains: mobility, self‐care, usual activity, pain/discomfort, and anxiety/depression. Each domain is scored on a 5‐point scale, which yields a descriptive system that can be combined into a five‐digit number reporting the patient's state of health. Each EQ‐5D‐5L health state can be converted to a single summary index by applying a formula that attaches weights to each level in each dimension. A number of formulae or value sets are available for different countries, based on the valuation of EQ‐5D health states from general population samples. In this study, the value set estimated for Spain by Ramos‐Goñi et al.^28^ will be used. After applying these weights, the range of the summary index is 1 (perfect health) to 0 (health state equivalent to death). Negative values represent health states considered to be worse than death. The questionnaire also includes a visual analogue scale where responders are asked to indicate their health status on the day of the interview, ranging from 0 (worst possible health) to 100 (best possible health).Catheter‐related quality of life questionnaire: To evaluate the specific health‐related quality of life for long‐term catheterized patients, Rethink Medical has developed two specific instruments created in the context of this project based on the experience of our previous studies (Patient's workshop).^25^ The first one (Data S5), administered during the initial visit, consists of 47 questions, related to the patient's experience and journey with catheterization before the study, as baseline data. The questions are related to the type of catheter and accessories used, the experience of catheterization, emotions felt at the beginning (right from the moment of the prescription), satisfaction and comfort with the catheter, complications associated with catheter use, usability and complications associated with accessories and changes in the personal habits caused by the catheter's use, and how these issues have affected their lives. The second one (Data S6), administered during the follow‐up visit, consists of the same questions as the first one (but referred to the catheter and accessories used during the study) plus four questions related to information received when catheterized for the first time (total 51 questions). In order to quantitatively evaluate the answers, statements will include single answers with scores on a scale from 0 to 10, 0 to 5, and 0 to 4 for both questionnaires. The questionnaire devised by Rethink Medical is expected to be validated during the clinical study in conjunction with another study specially designed for its validation.

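### For the quantitative primary endpoint, the all-randomised analysis is in effect an available-case analysis, nearly identical to the 4-week completers' analysis, and cannot show bias from outcome-related dropout

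*Protocol article*

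**What the plan says.** All references are to the protocol article.

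- **Populations (section 5.7).** The main set is defined thus: "The analysis population will consist of all patients who meet the selection criteria and are randomized". A second is then added: "additional analysis will be performed on patients who complete 4 weeks with the catheter".
- **Missing data (section 5.7).** "No imputation will be made for missing data".
- **Tests (section 5.7).** "A bivariate analysis will be carried out between the control–study groups with respect to the independent variables", with Student's t or Mann–Whitney U for quantitative variables. The sentence is about comparability of the groups. No other between-group test is named for the questionnaires.
- **Timing (Table 1, section 5.4).** The row "Quantitative data for QoL and catheter satisfaction" is marked at baseline and at 4 weeks, and nowhere else.
- **Content (section 5.4.1).** The first catheter questionnaire, "administered during the initial visit, consists of 47 questions", asks about catheterisation before the study. The 51-question version about the study catheter is given at the follow-up visit.
- **Leaving (section 5.2.1).** "Reasons for going off or discontinuing the trial are as follows": safety-threatening adverse events, antibiotics needed for reasons unrelated to the catheter, refusal and death. The section heading, however, also speaks of modifying the allocated intervention.
- **Early leavers (section 5.6).** All collected data are kept and used, and "Data from subjects who terminate the study earlier will also be included in a substudy analysis".

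**The concern.** Two analysis populations are normally specified so that one can check the other. Here the check depends on patients who stop early having an outcome, and the schedule gives them none. A patient who goes off the trial in week 2 has a baseline EQ-5D-5L and a baseline questionnaire about an earlier catheter, but no score for the study catheter. Without imputation, that patient drops out of the all-randomised comparison as well as the completers' comparison.

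The loss is plausibly related to the outcome. Refusal and device-related harm are likely to go with discomfort and dissatisfaction, which is what the endpoint measures. Patients and staff are unblinded (section 2.4), and the refusal clause describes an exchange only from T-Control to the conventional catheter, so refusal could differ by arm. An arm that loses its least satisfied patients looks better than it is. The qualitative primary endpoint does not compensate, because section 2.1 invites only patients who completed follow-up to the discussion groups.

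**Working it through.** **Inputs.** From section 5.3: 25 per group, standardised difference 0.95, significance level 2.5%, dropout 5%. Power and sidedness are not stated; I assume 80% and two-sided. Section 5.7 prints a different p-value threshold. That is a separate matter, and I use the 2.5% of the sample size section.

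**Step 1: the plan's own figure.** The exact t calculation for 0.95 SD at two-sided 2.5% and 80% power needs 23 per arm (power 81.3%). 23 / 0.95 = 24.2, rounded up to 25. The stated 25 per group reproduces and is not in dispute.

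**Step 2: expected losses.** At 5%, 25 × 0.05 = 1.25 patients per arm have no week-4 score. The chance of at least one in an arm is 1 − 0.95^25 = 72%. The binomial chance of three or more is 13%, and of five or more 0.7%.

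**Step 3: bias.** Suppose k of 25 patients in one arm have no score and would have scored δ SD worse than that arm's completers, whose mean is m. The arm's full mean is [(25 − k)m + k(m − δ)] / 25 = m − kδ/25. The available-case mean is m, so the bias is kδ/25. The documents give neither k nor δ; both are assumptions.

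With no true effect, the rejection probability at nominal two-sided 0.025 comes from the noncentral t with noncentrality b·√[25(25 − k)/(50 − k)], where b is the bias. For k = 5: 0.20 × √(500/45) = 0.67. Results for δ = 1, losses in one arm only:

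| k of 25 | Bias (SD) | Share of 0.95 | Rejection probability (nominal 0.025) |
|---|---|---|---|
| 1 | 0.04 | 4% | 0.026 |
| 2 | 0.08 | 8% | 0.030 |
| 3 | 0.12 | 13% | 0.037 |
| 5 | 0.20 | 21% | 0.057 |

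**Step 4: worst case.** Remove exactly the k lowest scores from one arm and none from the other. For normal scores the expected gain for k = 1, 2, 3, 5 is 0.08, 0.15, 0.22 and 0.34 SD. In 40,000 simulated null trials, the rate of false findings in favour of that arm was about 2.7%, 4.9%, 7.6% and 15.6%, against 1.25% nominal.

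**Step 5: balanced losses.** If each arm loses its lowest one or two scores, the mean bias is zero and the rate of false findings favouring T-Control is about 1.7% to 2.0%.

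**Step 6: do the planned analyses differ?** They differ only for patients whose catheter is removed or exchanged early but who still answer at week 4. The text of section 5.2.1 says off the trial and its heading allows a modified intervention, so such patients are possible but not provided for. The section 5.6 analysis can describe early leavers, but it cannot supply a week-4 score that was never collected.

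**The case against.** The strongest reply is that this is a self-described pilot with about 5% expected loss, that an available-case analysis is openly declared, and that an unseen SAP may add sensitivity analyses and define the early-leaver analysis. Much of this stands. The bias at planned dropout is small. Two of the listed reasons for leaving, death and antibiotics unrelated to the catheter, need not reflect dissatisfaction. The missing definition of the substudy is no finding, since it may sit in the SAP or full protocol. What remains is a rule that the article itself fixes: no imputation, applied to an endpoint measured once after randomisation.

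A reader might infer more than the documents support:

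- *That the two analyses contain exactly the same patients.* Section 5.2.1 is ambiguous, and the week-4 contact in section 5.2 is not made conditional on the study catheter still being in place. Nearly the same is as far as the text goes.
- *That the questionnaires are given only at week 4.* They are also given at baseline; only the post-randomisation measurement is single.
- *That every harmed patient disappears.* Only safety-threatening events lead off the trial. Pain, obstruction, leakage and haematuria are recorded as outcomes (section 5.4.2), and nothing says those patients leave. Section 5.6 keeps all collected data, and section 5.7 lists exclusions with reasons.
- *That a gain of 0.34 SD or a 16% false-positive rate is to be expected.* This needs five losses in one arm, all of them its lowest scores, and none in the other. At 5% dropout, five or more losses in an arm has a 0.7% chance.

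**Conclusion.** The point holds in this limited form. For the quantitative primary endpoint, the all-randomised analysis is in effect an available-case analysis, close to the completers' analysis, and agreement between the two would say nothing about outcome-related dropout. At the planned 5% the likely bias is about 0.04 to 0.08 SD, assuming one or two losses in one arm by patients 1 SD worse than its completers. It grows to about 0.20 SD with five of 25, and 0.34 SD is the worst case for that number. These sizes rest on assumed k and δ, normal scores with SD 1, and a two-sided 2.5% test.

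This does not invalidate the primary comparison. It is worth correcting because it is cheap, and because an imbalance in stopping would otherwise leave the result uninterpretable.

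**What to change.** 1. Keep the available-case analysis as primary. Amend the no-imputation sentence in section 5.7 to allow one prespecified sensitivity analysis of all randomised patients, for both questionnaires. Patients without a week-4 score who stopped through refusal or a device-related event receive the lowest (worst) rank across both arms, compared by Mann–Whitney. Scores missing for other reasons stay missing.
2. Report the number of missing week-4 scores and the reasons by arm.
3. Where the patient agrees, give the existing questionnaires at early termination, or at week 4 regardless of catheter status. Reconcile the heading and text of section 5.2.1 on whether a patient whose catheter is exchanged remains in follow-up.
4. Do not rely on multiple imputation with reason for stopping as a predictor. If stoppers have no week-4 score, the reason is seen only where the outcome is missing, so its effect cannot be estimated. Imputing from baseline and arm alone assumes data missing at random, which is the assumption in doubt. Ranking across both arms also avoids borrowing a worst score from the depleted arm.
5. Keep the section 5.6 substudy, the one analysis aimed at early leavers.

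The cost is one extra analysis per questionnaire and a line of SAP text. Stopping reasons are needed anyway for the listing of exclusions. Item 3 adds a questionnaire for a few patients. The downside is a less favourable or wider result if dropout is unbalanced.
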